#### Secondary outcomes

2.8.2

Secondary outcomes include pain acceptance, depression, anxiety, sexual function, and quality of life. To better our primary outcome measures, two other variables will also be analysed: unwillingness to perform the tampon test and abstinence from vaginal intercourse, both measured as binary variables.

Chronic pain acceptance questionnaire (CPAQ) is a self-assessment form used for patients with chronic pain and measures pain acceptance (Feliu-Soler et al., 2018; McCracken et al., 2004; Reneman et al., 2010). CPAQ is divided into two subscales: activity engagement (participation in activities despite living with pain) and pain willingness (attempts to avoid and control pain as pain management (ineffective coping) (Feliu-Soler et al., 2018; McCracken et al., 2004; Wicksell et al., 2009). The form consists of 20 statements that can be rated between “never true” to “always true”. CPAQ has good internal consistency and similar psychometric properties both when administered online or via paper-and-pencil (Fish et al., 2010; Wicksell et al., 2009).

The Female Sexual Function Index (FSFI) is an instrument for measuring female sexual function and consists of 19 questions within 6 domains: sexual desire, arousal, lubrication, orgasm, satisfaction, and pain (Rosen et al., 2000; Wiegel et al., 2005). Questions are rated on a Likert scale from 0 or 1 to 5, where 0 corresponds to no attempt at intercourse. Higher FSFI scores indicate better sexual functioning (Ter Kuile et al., 2006). Test-retest reliability has appropriate level of stability, while the internal consistency of the instrument and its subscales are satisfactory to good (Ter Kuile et al., 2006). The ability of the scale to predict the presence or absence of sexual complaints is considered excellent (Ter Kuile et al., 2006).

The Female Sexual Distress Scale-Revised (FSDS-R) is an instrument for measuring female sexual distress and consists of 13 questions (Derogatis et al., 2008). The score varies between 0 and 48 and each question can be rated from 0 (never) to 4 (always) (Derogatis et al., 2008). Higher FSDS-R scores indicate more sexual distress (Ter Kuile et al., 2006). The instrument has excellent reliability and good discriminant validity (Derogatis et al., 2008; Ghassami et al., 2014).

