### Statistical analysis plan

2.9

Linear mixed effect models will be used to assess the effect of the internet-based treatment on vulvar pain, pain acceptance, depression, anxiety, sexual function, and quality of life over time, by applying the intention-to-treat approach. Variables that vary significantly between groups at baseline will further be adjusted for in the model. Linear mixed modelling is a frequently recommended method for its abilities to handle missing data and correlated observations in repeated-measures data (Gueorguieva and Krystal, 2004; Yoo, 2010). The best-fitted model to the data consists of an unstructured covariance matrix using the restricted maximum likelihood (REML) estimation procedure. Baseline, posttreatment and follow-up measures will be used as repeated measures and intervention/control group will be used as fixed factors.

As significant drop-out is common in internet-based interventions, further analyses will be performed. Continuous data will be analysed with general linear models using besides intention-to-treat also per protocol approaches to assess the effects of the intervention on vulvar pain, depression, anxiety, sexual function, and quality of life at different time points (post-treatment and follow-up). Last observation carried forward (LOCF) will be used for the intention-to-treat analysis. Complementary analysis using worst case imputation and analysis using a per-protocol approach without imputation will also be carried out. Effect size will be calculated with Cohen's d. *P* values less than 0.05 will be considered statistically significant. Ordinal (impact of pain on sexual function) and binary data (willingness to perform tampon test and attempt at vaginal intercourse) will be analysed with Mann Whitney's test, Fischer's exact test and multivariate logistic regression, respectively, to assess differences between groups at posttreatment and follow-up. The binary data are referring to secondary outcomes and will be analysed using a per protocol approach only. Descriptive statistics at baseline and the corresponding changes during follow-up both will be provided in tables and graphically. All analyses will be completed using the IBM SPSS statistical package.

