Difficulties in recruiting are common in clinical trials and many trials may take longer to complete recruitment than primarily planned (Sully et al., 2013). Nevertheless, loss to follow-up seems to be a problem among internet interventions trials (Mathieu et al., 2013) and high dropout rates and low retention rates are a known issue among iCBT trials (Webb et al., 2017). An additional limitation of our study is the time period needed to conclude the recruitment phase, which has been prolonged due to dropouts and difficulties with retaining participants. To manage the issue of missing data, a per protocol approach will be used as a complement to ITT to facilitate interpretation of the findings (Beckett et al., 2016). Whilst ITT analysis has the advantage to preserve the balance afforded by randomisation, minimising the risk of for type I error and resembling clinical practice (Beckett et al., 2016; McCoy, 2017), a per-protocol approach may provide the true efficacy of an intervention among completers. LOCF is a common imputation method, but it has previously been criticized for overestimation of values as the true mean differences are not present when dropout rates differ between groups (Gueorguieva and Krystal, 2004; Lachin, 2016). Therefore, worst case imputation will be used to avoid inaccurate estimates and ensure the trustworthiness of the results.

Further, the specific limitations and practical problems encountered in this study may be of use for clinicians planning to implement this material. These should be taken into consideration when adjusting the content for use in clinical settings. A study involving qualitative analysis would be of value to further explore this issue and is now under way, which may have an impact on the planning of future studies.

At this point, there is a considerable knowledge gap when it comes to internet-based treatment for patients with vulvodynia. If effective, internet-delivered psychological treatment can easily be adapted and used in clinical settings to complement clinical treatment in a primary care setting.

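### The two binary outcomes that support the primary pain measure are compared per protocol only, so the comparison is not of the groups as randomised

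*Protocol article*

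**What the plan says.** The protocol article, section 2.8.2 (Secondary outcomes), introduces the two variables to strengthen the primary measure: "To better our primary outcome measures, two other variables will also be analysed: unwillingness to perform the tampon test and abstinence from vaginal intercourse". Both are binary.

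Section 2.9 (Statistical analysis plan) tests them "to assess differences between groups at posttreatment and follow-up" and fixes the analysis set: "The binary data are referring to secondary outcomes and will be analysed using a per protocol approach only".

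The same section treats the continuous outcomes differently. They get a mixed model by intention-to-treat, and in addition: "Continuous data will be analysed with general linear models using besides intention-to-treat also per protocol approaches". Last observation carried forward and worst-case imputation are planned for them. Of per protocol it says: "analysis using a per-protocol approach without imputation will also be carried out".

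The Discussion (section 5) gives the rationale. On one side: "Whilst ITT analysis has the advantage to preserve the balance afforded by randomisation". On the other: "a per-protocol approach may provide the true efficacy of an intervention among completers". It presents per protocol as something used alongside intention-to-treat.

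**The concern.** The word *only* leaves no intention-to-treat version of these two comparisons. This is a stated rule, not a detail left to a fuller document.

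The two outcomes carry more weight than their secondary label suggests. The primary outcome is pain at intercourse and at the tampon test (section 2.8.1). A woman who declines the test or abstains has no current experience to score, so these variables help to show who stands behind the pain scores. If they are compared only in a subset formed after randomisation, a difference between arms may reflect who stayed in the subset rather than what the treatment did. Avoidance could plausibly influence both the outcome and staying in the set, since modules 2 to 6 include exposure exercises (Table 1).

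**Working it through.** **1. Is the stated reason consistent with the rest of the plan?** The reason given is that the outcomes are secondary. Depression, anxiety, sexual function and quality of life are also secondary (sections 1.2 and 2.8.2), and section 2.9 analyses them by intention-to-treat as well as per protocol. Secondary status therefore does not separate the two binary outcomes from the others. The Discussion's account of per protocol as an addition also fails for them, because there is no intention-to-treat analysis for it to be added to.

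**2. How much loss is in view?** The plan gives no size or power figure for the binary outcomes, so there is none to reproduce. Its 26 per group refers to pain, with 20% dropout assumed (section 2.7). For the first 15 women, section 2.6 reports 33% loss by T1 (5/15) and a 47% figure at T2. Applied to 26 per arm:
- T1: 26 × 0.67 = 17.4, about 17.
- T2, if 47% is of T1 responders, as worded: 26 × 0.67 × 0.53 = 9.2, about 9.
- T2, if 47% is of baseline: 26 × 0.53 = 13.8, about 14.

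Both T2 readings are shown because 47% of 10 women is 4.7, not a whole number, while 7/15 is 47%. None of these figures is split by arm.

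**3. When does selection produce a difference with no treatment effect?** Let p be the share truly willing, the same in both arms. Let k be the chance that a willing woman stays in the analysed set divided by the chance that an unwilling woman does. The share willing among those kept is

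p′ = p·k / (p·k + 1 − p).

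The spurious difference is p′ in the intervention arm minus p′ in the control arm. The documents give neither p nor k; both are assumptions. With p = 0.5:
- k = 1 in both arms: 0.50 − 0.50 = 0.
- k = 2 in both arms: 0.667 − 0.667 = 0.
- k = 1.5 in the intervention arm only: 0.75/1.25 = 0.60, so +10 points.
- k = 2 in the intervention arm only: 1.0/1.5 = 0.667, so +17 points.
- k = 1.5 or 2 in the control arm only: −10 or −17 points.

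Across p = 0.3, 0.5 and 0.7, selection in one arm only gives 8 to 10 points at k = 1.5, 12 to 17 at k = 2 and 18 to 26 at k = 3.

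**4. What does that do to the test?** Exact two-sided Fisher rejection probabilities at 0.05, no true effect, p = 0.5:
- 26 v 26, all randomised, complete data: 2.5%.
- 17 v 17, selection in the intervention arm only: 4.9% (k = 1.5) or 9.8% (k = 2).
- 17 v 26, selection in the intervention arm only: 6.5% (k = 1.5) or 13.7% (k = 2).

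Over the feasible combinations of the three values of p with retention of 35.5%, 53% or 67%, the rates are 1.9–7.4% at k = 1.5, 2.7–14.8% at k = 2 and 4.0–32.5% at k = 3. The estimate can therefore be biased while the test stays below 5%. For scale, the standard error of the difference at 17 v 17 and p = 0.5 is √(2 × 0.25/17) = 0.17, as large as the shift at k = 2.

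**The case against.** A reader might infer that exclusions fall on the intervention arm alone, because only that arm has modules to complete, and that the plan therefore builds in a gain of predictable size for the treatment. The documents do not support this. The per-protocol set is nowhere defined as module adherence. Section 2.9 describes it as done without imputation, and the Discussion ties it to missing data and to completers. That fits women who answered the assessment, a rule that can remove women from either arm. Parallel clinical treatment, which is checked in medical records (section 2.6), could also count as a deviation in either arm. Nothing shows that avoidant women leave the intervention arm more often, or that untreated controls do not leave more.

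A reader might also infer that these two outcomes are the only check on selective missingness in the pain scores. They are not. Worst-case imputation is planned. The FSFI has a zero category for no attempt, and sexual function is analysed by intention-to-treat. The pain-impact item has a grade for pain that prevents intercourse.

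The Discussion's sentence on efficacy is also hedged and limited to completers, so it is not a flat claim that per protocol gives the right answer.

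All of this stands, and it limits the point. It supplies no reason for withholding an intention-to-treat analysis from these two outcomes.

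**Conclusion.** The point holds as a narrow one. Section 2.9 gives up the randomised comparison for two outcomes meant to support the primary measure, for a reason that the plan does not apply to its other secondary outcomes.

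Bias under no effect requires selection that is related to the outcome and differs between arms. That is plausible but not shown, and neither its size nor its direction follows from the documents. The shifts of 8 to 26 points rest wholly on assumed willingness rates and on retention ratios of 1.5 to 3 in one arm only; with equal ratios the shift is zero. Even with equal selection, the estimate would describe those kept in the set, not all women randomised.

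It would be too strong to conclude that the trial's main result is compromised. The primary pain scores have their own mixed model by intention-to-treat, with carried-forward and worst-case analyses, and none of these depends on this rule.

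**What to change.** In section 2.9, make the main analysis of both binary outcomes one of all randomised women as allocated. Use the logistic regression already planned, at T1 and at T2, adjusted for the woman's own status at T0, which section 2.8.2 says is collected. Count missing answers as unwilling or no attempt in both arms, in line with the worst-case approach planned for the continuous data. Add an available-case analysis as sensitivity, and keep per protocol as supportive only.

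The sensitivity analysis is needed because the missing-answer rule is itself an assumption. If 50% were willing in both arms and 80% of one arm but 67% of the other answered, unrelated to willingness, the rule would show 0.5 × 0.80 = 40% against 0.5 × 0.67 = 33.5%, a gap of 6.5 points with no effect. Reading the two analyses together shows how far the result depends on non-response.

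Multiple imputation or a complier-average estimate could be added, but neither is needed to correct the point. The cost is a change of wording, a few extra model runs and possibly a less favourable estimate. No new data are required.

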## Patient and public involvement

3

This study is performed without participant involvement apart from the feedback received during the pilot phase (data not published), that was implemented in order to assess the feasibility of the study. The pilot study was conducted among patients who had contacted the hospital in the past because of vulvodynia. The study content was adjusted after comments from these participants. Otherwise, participants in the present study are not invited to comment on the study design, interpret the results, or contribute to the writing or editing of this document for accuracy.

## Ethics, data management and dissemination

4

The EMBLA study has been approved by the regional ethical review board in Uppsala, Sweden (registration number 2015/031), and is registered at clinicaltrials.gov (protocol ID EMBLA, ID NCT02809612). The study is conducted following the principles of the Declaration of Helsinki.

In addition to the information provided over the telephone, written information about the EMBLA study is sent to all women who are interested in participating in the study. Eligible participants are asked to provide written informed consent. Each participant is assigned a code and the data included in the database cannot be traced back to any individual participant. All data are thus coded and stored securely on Uppsala University's servers. The code key is stored separately on a different folder in the secure server. All consent forms are archived in locked spaces.

The results of this trial will be disseminated in peer-reviewed publications and as presentations at international conferences.

## Discussion

5

Internet-based treatment would also enable participants from different and often remote geographic areas to receive treatment. In Sweden, most of 97% of the population has access to fast internet (Internet World Stats, 2019). The study's results are expected to be of value in the planning of clinical care in the medical area.

As a randomised controlled trial with short- and long-term follow-up points, the EMBLA study intends to provide a novel and better understanding regarding the treatment of vulvodynia and the role of internet-based treatment as a complement to standard care for women suffering from vulvodynia. The use of a randomised controlled design and the use of well-accepted validated self-assessment questionnaires are strengths in our study.

Selection from a clinical setting and access to participants' medical records to control for concomitant treatments and other variables is also a strength in our study. The risk for diagnostic misclassification is low, as the diagnosis of vulvodynia has to be confirmed in a screening interview. Guidance may facilitate adherence to treatment and is important to increase efficacy (Baumeister et al., 2014; Webb et al., 2017). A limitation may be the eCoaches varying professional experience with CBT treatment with ACT components. However, the qualification of eCoaches has minor importance for the outcome (Baumeister et al., 2014). Further, the differences in previous experiences are minimised by using message templates and by the possibility to discuss with senior researchers (Lattie and Graham, 2019).

Difficulties in recruiting are common in clinical trials and many trials may take longer to complete recruitment than primarily planned (Sully et al., 2013). Nevertheless, loss to follow-up seems to be a problem among internet interventions trials (Mathieu et al., 2013) and high dropout rates and low retention rates are a known issue among iCBT trials (Webb et al., 2017). An additional limitation of our study is the time period needed to conclude the recruitment phase, which has been prolonged due to dropouts and difficulties with retaining participants. To manage the issue of missing data, a per protocol approach will be used as a complement to ITT to facilitate interpretation of the findings (Beckett et al., 2016). Whilst ITT analysis has the advantage to preserve the balance afforded by randomisation, minimising the risk of for type I error and resembling clinical practice (Beckett et al., 2016; McCoy, 2017), a per-protocol approach may provide the true efficacy of an intervention among completers. LOCF is a common imputation method, but it has previously been criticized for overestimation of values as the true mean differences are not present when dropout rates differ between groups (Gueorguieva and Krystal, 2004; Lachin, 2016). Therefore, worst case imputation will be used to avoid inaccurate estimates and ensure the trustworthiness of the results.

Further, the specific limitations and practical problems encountered in this study may be of use for clinicians planning to implement this material. These should be taken into consideration when adjusting the content for use in clinical settings. A study involving qualitative analysis would be of value to further explore this issue and is now under way, which may have an impact on the planning of future studies.

At this point, there is a considerable knowledge gap when it comes to internet-based treatment for patients with vulvodynia. If effective, internet-delivered psychological treatment can easily be adapted and used in clinical settings to complement clinical treatment in a primary care setting.
